### Secondary analyses

*Secondary efficacy outcomes:* Additional covariates adjusted regression models will examine differences in secondary acute outcomes (opioid use; T2), and secondary chronic outcomes (HRQL, anxiety, depressive symptoms, sleep quality, opioid misuse; T3) between the relevant treatment arms (as noted in primary analyses).

*Exploratory analyses:* Additional logistic analyses will compare rates of CPSP, a binary variable based on pain intensity and HRQL, at 3 months and 6 months in youth receiving combined pre- and post-operative CBT (arm 4) compared to arms 1, 2, and 3. We will also explore extent through which acute post-operative pain intensity and interference (T2) as well as changes in psychosocial factors (sleep quality, anxiety, and depression; T2-T4 relative to T1) exert their influence on (i.e., mediate) change in pain intensity, HRQL, and pain interference at 3 months follow-up using a structural equation modeling (SEM) approach.

Effect modification will be examined through regression models with interactions and subgroup analysis testing whether there are differential intervention effects across sex, racial, and ethnic groups on primary and secondary acute and chronic outcomes.

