### Objectives

This multicenter randomized controlled trial (RCT) aims to test the effectiveness of a digital CBT intervention called “SurgeryPal” in a factorial design comparing SurgeryPal^TM^ delivered to adolescents and their parents during one or both peri-operative phases (pre- vs. post-surgery) relative to online education (to control for participants’ time and attention). As recommended by PedIMMPACT, primary outcomes are acute and chronic pain severity and interference [27]. Secondary outcomes include HRQL, psychosocial distress, sleep disturbance, and opioid use/misuse. An additional aim will explore mechanisms of intervention effect on preventing CPSP, including reductions in acute pain severity and psychosocial distress.

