### Primary outcome measures

*Pain severity and interference.* Primary acute and chronic outcomes will be assessed using the 24-h (short) version of the Brief Pain Inventory (BPI), a validated patient-reported outcome measure comprised of a pain severity scale (4 items) and a pain interference scale (7 items) [30]. Adolescents will complete this measure daily for 14 days beginning on day 1 after hospital discharge (T2) and will complete the measure daily for 7 days at the follow-up assessments (T3 and T4). Adolescents rate worst, least, average, and current pain severity and rate pain interference on activity, mood, walking, work/school, relations, sleep, and enjoyment of life in the preceding 24 h. Responses are indicated on numerical rating scales with anchors 0 = “No Pain”/“Does not Interfere” and 10 = “Pain as bad as you can imagine”/“Completely Interferes”. The pain severity scale (average of 4 items) and pain interference scale (average of 7 items) will be calculated for each diary day completed. The BPI has been used to assess postsurgical pain intensity and interference in adolescents after major surgery [31].

The acute pain primary outcomes (*acute pain severity and interference)* will be derived as the individual rate of recovery based on BPI trajectories separately for pain severity and pain interference over 14 days immediately post-discharge (T2). The chronic pain primary outcomes (c*hronic pain severity and interference*) will be assessed as the mean of the participant’s daily pain ratings on the BPI separately for pain severity and pain interference at 3 months post-surgery (T3).

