### Secondary outcome measures

Table 3 provides details on the secondary outcome measures.

**Table 3 Tab3:** Secondary outcomes measures

Measure	Description	Respondent	Time point			
			T1	T2	T3	T4
Pediatric Quality of Life Inventory - Short form, acute version^a^ [32, 33]	15-item measure assessing health-related quality of life (HRQL) over the last 7 days across the following domains/subscales: physical health, psychosocial health, and total HRQL, reported on a 5-point Likert scale.	Adolescent	✔		✔	✔
Opioid use [30]	2 items on the BPI assessing daily opioid use and pain relief from medications. Acute opioid use will be calculated as the number of days of opioid use during 14 days daily monitoring (T2).	Adolescent	✔	✔	✔	✔
NIDA-Modified ASSIST Tool^a^ [34, 35]	15-item measure assesses alcohol, smoking, substance, and opioid misuse in the past 2 weeks; additional questions about reasons for misuse (e.g., to treat pain, to get high, etc.) and source of opioids (e.g., prescription, from a friend or relative) will be used from the National Survey on Drug Use and Health [36].	Adolescent	✔		✔	✔
PROMIS Pediatric Anxiety SF8a [37]	8-item measure used to assess adolescent self-reported anxiety. Adolescents endorse frequency of fear, anxiety, hyperarousal, and somatic symptoms experienced in the prior 7 days, on a 5-point Likert scale.	Adolescent	✔		✔	✔
PROMIS Pediatric Depression SF8a [37]	8-item measure assess depressive symptoms. Frequency of negative mood, negative views of self, decreased positive affect, and decreased engagement in the prior 7 days reported on a 5-point Likert scale.	Adolescent	✔		✔	✔
Patient Health Questionnaire-4^a^ [38]	4-item screening measure of general anxiety and depressive symptoms experienced in the preceding 2 weeks by the respondent.	Adolescent, parent	✔		✔	✔
Pain Catastrophizing Scale – Child Version^a^ [39]	13-item measure that assesses child pain catastrophizing. Adolescents report frequency of symptoms of rumination, magnification, and helplessness experienced when in pain using a 5-point Likert scale.	Adolescent	✔		✔	
Pain Catastrophizing Scale – Parent Version^a^ [40]	13-item measure that assesses parents’ symptoms of rumination, magnification, and helplessness, in response to their child experiencing pain, on a 5-point Likert scale.	Parent	✔		✔	

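### In the exploratory mediation model, two of the seven BPI interference items overlap in content with the sleep and mood mediators, and the article names no check for this

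*Protocol article*

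**What the plan says.** All references are to the protocol article.

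- **Aim.** Under Objectives: "An additional aim will explore mechanisms of intervention effect on preventing CPSP, including reductions in acute pain severity and psychosocial distress".
- **Mediators.** Secondary analyses (exploratory paragraph) names acute pain intensity and interference after discharge, and "changes in psychosocial factors (sleep quality, anxiety, and depression; T2-T4 relative to T1").
- **Outcomes.** The same sentence asks how far these "mediate) change in pain intensity, HRQL, and pain interference at 3 months follow-up", by structural equation modelling.
- **Interference score.** Under Primary outcome measures, adolescents "rate pain interference on activity, mood, walking, work/school, relations, sleep, and enjoyment of life in the preceding 24 h". Scoring is unweighted: the "pain interference scale (average of 7 items) will be calculated for each diary day completed".
- **HRQL.** Table 3 lists "domains/subscales: physical health, psychosocial health, and total HRQL". The exploratory paragraph says only HRQL and does not name the score.
- **Mediator scales.** Table 3 gives separate adolescent-report instruments: a sleep scale covering the past month, and PROMIS anxiety and depression scales covering the past week. All three are scheduled at T1, T3 and T4, and none at T2.

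The article does not say how content shared between mediators and outcomes will be handled.

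**The concern.** Sleep and mood are on both sides of the path from mediator to interference. Suppose CBT improves sleep and mood, and adolescents therefore report less interference with sleep and mood but no change in the other five activities. The seven-item mean still falls, and its association with the mediators produces an indirect effect. The natural reading would be that better sleep and less distress reduced pain-related disability, when function outside sleep and mood had not changed.

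Two features of this trial make the question worth settling in advance:

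- The intervention is aimed at distress and sleep (Adolescent CBT intervention), so an effect of treatment on the mediators is what the investigators expect.
- With no T2 measure of these mediators, and T4 falling after the 3-month outcome, the only usable post-treatment measure is T3. That is the same assessment as the outcome and comes from the same respondent, so time order cannot help to separate shared content from cause.

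What is at stake is the interpretation of the mechanism aim for one outcome, not any test of treatment effect.

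**Working it through.** The article states no figure for the mediation analysis, so there is none to reproduce.

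**1. Weight of the overlapping items.** Mood and sleep are two of seven equally weighted items: 2/7 = 28.6%. Counting enjoyment of life as well gives 3/7 = 42.9%, but that item is not a named mediator construct, so I use 2/7.

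**2. Share of an indirect effect carried by those items.** Let *a* be the effect of treatment on the mediator, *L* the slope of the mood and sleep items on the mediator, and *b* the slope of the other five items.

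Indirect effect on the seven-item mean = *a*(2*L* + 5*b*)/7

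Share from mood and sleep = 2*L*/(2*L* + 5*b*)

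| *b* relative to *L* | Share |
|---|---|
| *b* = *L* | 2/7 = 28.6% |
| *b* = *L*/2 | 2/4.5 = 44% |
| *b* = *L*/4 | 2/3.25 = 62% |
| *b* = 0 | 100% |

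The documents give neither slope, so the true share is unknown.

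**3. Could the overlap alone give a significant result?** This simulation rests on assumed inputs: one composite mediator with within-group SD 1, *a* = 0.3, *b* = 0, two equal groups, and significance declared when both paths have |z| above 1.96, with 1000 runs per setting. The total of 400 is the target complete sample; 200 corresponds to two arms of 100.

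| *L* | 7 items, N = 400 | 5 items, N = 400 | 7 items, N = 200 | 5 items, N = 200 |
|---|---|---|---|---|
| 0 | 5.1% | 4.6% | 2.7% | 2.8% |
| 0.2 | 29.0% | 3.9% | 10.1% | 2.3% |
| 0.4 | 71.6% | 3.6% | 33.1% | 2.9% |
| 0.6 | 83.3% | 4.6% | 48.3% | 1.6% |
| 0.8 | 85.7% | 5.4% | 55.8% | 2.9% |

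**4. Checks on the simulation.** The seven-item rate cannot exceed the power of the treatment-to-mediator path. At N = 400 the standard error is √(1/200 + 1/200) = 0.1, so z = 0.3/0.1 = 3 and power = Φ(3 − 1.96) = Φ(1.04) = 85%. This matches the ceiling at high *L*. The expected indirect effect at *L* = 0.4 is 0.3 × 2 × 0.4/7 = 0.034, and the simulated mean was 0.034.

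The effect produced this way is small in absolute terms. The risk is a significant result that is misread, not a large spurious effect.

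**The case against.** The strongest case against has four parts.

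- **The items differ from the mediators.** The BPI asks how far pain interfered with mood or sleep over 24 hours. The mediators are separate scales with other recall periods, and no BPI item asks about anxiety. This stands. A reader might infer that mediation is guaranteed by construction, and the documents do not support that: treatment must move the mediators, and the mediator scales must track the BPI items.
- **The size is unknown.** This also stands. The simulation shows what can happen under assumed slopes, not what will happen. Any specific fall in the mood and sleep items, converted to points on the interference score, would be an invented input.
- **HRQL and pain intensity.** A reader might extend the point to HRQL as a second compromised outcome. The article does not say which HRQL score enters the model and does not show the psychosocial items, so that overlap is only a possibility. Pain intensity has no mood or sleep items and is unaffected, as are the paths through acute pain to pain intensity. The mechanism aim therefore does not fail as a whole.
- **This is analysis-plan detail for an exploratory analysis.** It is partly so, and the analysis plan, which is not shown, may deal with it. However, the article itself pairs these mediators with this outcome and fixes the outcome's items and scoring. The overlap follows from what it states.

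The objection reduces the size and certainty of the point but does not remove it.

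**Conclusion.** The point holds in limited form. Mood and sleep items carry 2/7 (29%) of the interference outcome, while changes in sleep quality, anxiety and depression are its proposed mediators. A significant indirect effect could arise from those two items alone, and the model as described could not reveal this. Their share of any indirect effect is 29% if all items respond equally and more if the other five respond less.

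The first figure follows from the article's item list and scoring, taking the 3-month change as based on the same seven items. The share formula assumes linear slopes, equal across the two overlapping items and across the other five.

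This is a minor matter of interpretation, confined to one exploratory outcome, with a conditional extension to HRQL if the total score is used.

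**What to change.** Keep the full seven-item score for the primary comparisons and for the main mediation model. Replacing it there would leave the model explaining something other than the primary outcome. Add before analysis:

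- **A sensitivity model** in which interference is the mean of the five items other than mood and sleep: activity, walking, work/school, relations and enjoyment of life.
- **If total HRQL is the outcome,** the same model for the physical-health subscale, reported beside it.
- **A reporting rule:** claim mediation of pain-related functioning only if the indirect effect persists in the sensitivity model, judged from the estimate and its interval as well as its significance. Persistence removes the shared-content explanation but not the limitation that mediator and outcome are both measured at T3.

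Cost: about one sentence of analysis-plan text and one extra exploratory analysis. The items and subscale are already collected. The five-item score is non-standard and somewhat less reliable, so some loss of precision should be expected and should not by itself be read as absence of mediation.

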### Sample size and power calculations

Power calculations on primary pain outcomes are based on data available from our preliminary peri-operative studies [4, 7, 31] and from prior peri-operative intervention studies [16–18]. Power analyses for primary acute outcomes were based on rate of recovery using an exponential decay model. Based on pilot data, we assume log(rate) = − 1.21 (SE = 0.38) in the intervention arm, which translates into a half-life (days taken to achieve 50% reduction in BPI outcome from time 0) of 4.13 days. Using a conservative estimate of 35% increased half-life of recovery in the control arm, 31 subjects per arm would provide 90% power; N = 24/arm for 80% power.

For the second acute parameter of interest, power calculations were performed using GEE model on time-averaged difference (TAD) using individual daily repeated measures of BPI scores. In order to detect a group difference of 1.2 with standard deviation 2.0, we need to enroll 199 participants into each of the two comparison groups (total sample of 398; assuming 1:1 allocation of subjects into pre-operative education vs. intervention, within-subject observations follow AR(1) correlation pattern with a correlation coefficient of 0.7, and a missing completely at random rate of 5% each day).

For the primary chronic pain outcomes, to detect a group difference of 1.0 with standard deviation 1.8, 35 subjects are needed per arm for 80% power based on two-sample t test.

The target complete sample is 400 adolescent/parent dyads. Conservatively accounting for 20% attrition, we plan to enroll 500 adolescents but will adjust this if completion rates are > 80%.

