### Primary efficacy outcomes

*Hypothesis 1 (acute outcomes): Adolescents receiving pre-operative CBT will have a faster rate of recovery of pain severity and interference during the 14 days following hospital discharge, compared to adolescents who receive pre-operative education.* The acute outcomes will be assessed before any post-operative intervention has taken place. Therefore, arms 1 and 3 will be combined into the control group (pre-operative education); arms 2 and 4 will be combined into the intervention group (receiving pre-operative CBT intervention) for this analysis (see Table 4). We will apply nonlinear mixed effects models with an exponential decay functional form, to evaluate individual rate of recovery in daily pain severity and interference, or how quickly the process decays/improves from the initial value to the asymptote. Rate parameters will be estimated using restricted maximum likelihood (REML) approach and compared using multivariate Wald test. As a further primary analysis, we will treat daily pain severity and interference as repeated measures using generalized estimating equations (GEE) to account for clustering within participants.

**Table 4 Tab4:** Treatment arms

Group	Pre-operative phase	Post-operative phase
1	ED	ED
2	CBT	ED
3	ED	CBT
4	CBT	CBT

*ED* online education, *CBT* Cognitive Behavioral Therapy Intervention

*Hypothesis 2 (chronic outcomes): Adolescents receiving post-operative CBT alone will have lower pain severity and interference, compared to adolescents receiving education control at 3 months.* We will consider the education control arm (arm 1) as the control group and post-operative CBT alone arm (arm 3) as the intervention group. Covariates adjusted linear regression models will examine group differences in average pain severity and interference, as continuous outcomes, at 3 month follow-up.

*Hypothesis 3 (chronic outcomes): Adolescents receiving both phases of peri-operative CBT will have lower pain severity and interference compared to adolescents receiving single phase (pre- or post-surgery) intervention or education control alone at 3 months.* We will apply linear regression models to examine differences in average pain severity and interference between individual study arms, treated as a 4-level categorical predictor variable.

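### The two acute sizing effects are not reconciled: with a common start and asymptote, a 35% longer control half-life gives at most 0.92 points over 14 days, not 1.2, and 199 per group is not the size for 1.2

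*Protocol article*

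**What the plan says.** Under Sample size and power calculations, the acute outcome is sized twice.

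- **Rate of recovery.** The intervention arm is given log(rate) = −1.21, "which translates into a half-life (days taken to achieve 50% reduction in BPI outcome from time 0) of 4.13 days". Then: "Using a conservative estimate of 35% increased half-life of recovery in the control arm, 31 subjects per arm would provide 90% power".
- **Time-averaged difference by GEE.** The target is worded "In order to detect a group difference of 1.2 with standard deviation 2.0". The resulting size is 199 per pooled group, 398 in all. The stated conditions are 1:1 allocation, AR(1) correlation of 0.7 and 5% of days missing completely at random. No alpha or power level is given for this calculation.

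Under Primary efficacy outcomes, Hypothesis 1 predicts a "faster rate of recovery of pain severity and interference during the 14 days following hospital discharge". It covers both analyses, and the GEE model is named as an additional primary analysis. Both compare arms 2 and 4 with arms 1 and 3. Under Primary outcome measures, the BPI scales run from 0 to 10 and are completed daily for 14 days from the first day after discharge. No starting score or asymptote is given for the decay model.

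**The concern.** The two calculations use the same diary scores and the same contrast, under one hypothesis worded as a difference in rate. The section gives a cautious relative effect for one and an absolute difference for the other, and does not connect them. A rate effect of a given size implies a difference in the 14-day mean once the starting score and asymptote are set, so the two can be compared.

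If they disagree, a reader cannot tell what effect the GEE analysis is planned to detect, or what power it has if CBT works as the rate calculation assumes. An observed GEE difference of about 0.4 points could be read as a third of plan (0.4 / 1.2) when it may be what the half-life assumption predicts.

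**Working it through.** **Inputs from the protocol article.** Half-life 4.13 days; control half-life 35% longer; log(rate) −1.21; difference 1.2; SD 2.0; AR(1) 0.7; 5% of days missing; 14 days; 199 per group; scale 0–10.

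**Assumptions not in the document.** Two-sided alpha 0.05; 80% or 90% power for the GEE calculation; starting scores of 4 to 8; asymptote 0 or 29% of start; common start and asymptote in both arms.

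**Step 1: try to reproduce 199.** The variance of a 14-day mean, as a multiple of SD², is f = Σᵢ Σⱼ pᵢⱼ 0.7^|i−j| / (14 × 0.95)², with pᵢⱼ = 0.95 when i = j and 0.95² otherwise. This gives f = 0.330 (0.326 with no missing days).

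n per group = 2 × SD² × f × (z₁ + z₂)² / 1.2²

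- 80% power: 8 × 0.330 × 7.849 / 1.44 = 14.4, so 15.
- 90% power: 8 × 0.330 × 10.507 / 1.44 = 19.2, so 20.
- One observation per adolescent (f = 1): 44 and 59.

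None of these is near 199. In the other direction, SE at 199 per group = √(8 × 0.330 / 199) = 0.115. The detectable difference is 2.802 × 0.115 = 0.32 at 80% power and 3.242 × 0.115 = 0.37 at 90%.

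**Step 2: the difference implied by the 35% assumption.** With start I and asymptote 0, the 14-day mean is I × mean over t = 1..14 of exp(−kt).

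- Intervention: k = ln 2 / 4.13 = 0.1678; mean 0.3536 × I.
- Control: half-life 4.13 × 1.35 = 5.58 days, k = 0.1243; mean 0.4449 × I.
- Difference: 0.0913 × I, or 0.37, 0.46 and 0.55 points for starts of 4, 5 and 6, and 0.91 for a start of 10.

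A difference of 1.2 would need I = 1.2 / 0.0913 = 13.1, which is off the scale. With the ratio held at 1.35, the largest value over all half-lives is 0.0923 × I (half-life about 4.8 days), or 0.92 points from a start of 10. A common non-zero asymptote multiplies the difference by (1 − asymptote / start) and so only shrinks it.

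**Step 3: what would give 1.2.**

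- Common start, asymptote 0, half-life 4.13 days: a half-life ratio of 1.48 (start 10), 1.75 (start 7), 1.93 (start 6) or 2.22 (start 5).
- Ratio held at 1.35: a control start higher by about 1.1 points (intervention start 8) to 1.9 points (intervention start 4).

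**Step 4: power of the GEE analysis for the implied difference.** Power = Φ(difference / 0.115 − 1.96), at 199 per group. The stated rate exp(−1.21) = 0.298 per day gives ln 2 / 0.298 = 2.32 days if the asymptote is 0. It gives 4.13 days to half the starting score only if the asymptote is about 29% of start. Three cases are therefore shown.

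| Case | Start 4 | Start 5 | Start 6 |
|---|---|---|---|
| Half-life 4.13 d, asymptote 0 | 0.37, 89% | 0.46, 98% | 0.55, 99.7% |
| Rate exp(−1.21), asymptote 0 | 0.29, 72% | 0.37, 89% | 0.44, 97% |
| Rate exp(−1.21), asymptote 29% of start | 0.21, 44% | 0.26, 62% | 0.31, 77% |

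At 1.2 points, difference / SE is 10.4, so power is essentially 100%.

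**The case against.** The protocol never says that the arms share a starting level or asymptote. Pre-operative CBT precedes surgery and the diaries begin after discharge, so the arms could already differ on day 1. That shift would enter a time-averaged difference but not a rate. The 35% is called conservative, and Hypothesis 1 gives no magnitude. The section calls the time-averaged difference a second parameter, cites several studies as the basis for its calculations, and does not derive 1.2 from the half-life. Under the stated inputs, 199 per group is often ample for the implied difference.

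Much of this stands, and it rules out three stronger readings that a reader might infer:

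- **That Hypothesis 1 cannot produce 1.2.** It can, with a larger half-life ratio or a difference in starting level (Step 3).
- **That the trial was sized for 1.2 and is underpowered as a result.** The 199 is far more than 1.2 requires, and power is about 89% or more for starts of 4 or above at 4.13 days and asymptote 0. The low figures need both a low assumed start and an inferred asymptote.
- **That a quoted GEE power is overstated.** None is quoted.

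What the objection does not remove is the gap between the figures. The section states no starting difference and no half-life ratio above 1.35, and Hypothesis 1 speaks only of rate. Separate sources could explain 1.2, but they would not make it the size that 199 delivers.

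**Conclusion.** The point holds in a conditional form. Given a common start and asymptote, 1.2 points and a 35% longer half-life are not the same effect: the latter gives at most 0.92 points, and 0.37 to 0.55 for starts of 4 to 6 at 4.13 days and asymptote 0. The section states nothing that bridges the gap. Separately, 199 per group does not follow from 1.2 with SD 2.0, AR(1) 0.7 and 5% missing. The difference, the SD, the correlation or the sample size is misstated, and the document does not show which.

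The consequence is an unreconciled sizing statement for a primary analysis, not a demonstrated shortfall in sample size. Across the assumed starts of 4 to 6, GEE power for the implied difference ranges from about 44% to over 99%. Where it lies depends on the starting score and asymptote, which the pilot data should supply. All power figures assume two-sided 0.05.

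**What to change.** Rewrite the GEE paragraph under Sample size and power calculations:

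1. State alpha and power, and give the time-averaged difference detectable at about 200 per group. With the present SD, correlation and missingness this is about 0.32 points at 80% power and 0.37 at 90%. If one of those inputs is the misstated item, correct it and recompute.
2. Give the pilot starting score and asymptote, derive the 14-day mean difference that the 35% half-life assumption implies, and state the GEE power for it.
3. If 1.2 is kept, justify it separately and state the starting-level difference or larger half-life ratio behind it. If a starting-level difference is expected, add it to Hypothesis 1, which now claims only a faster rate.

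The cost is one paragraph, plus a phrase in Hypothesis 1 if the third route is taken. Enrolment and data collection do not change. The stated effect for the GEE analysis will probably look less favourable than 1.2.

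### The acute time-averaged-difference calculation states 199 per group, but its own inputs need about 15 to 20, and it is the only calculation near N = 400

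*Protocol article*

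**What the plan says.** The section Sample size and power calculations gives three calculations. The second concerns the time-averaged difference in daily BPI scores, analysed by GEE. It states that "to detect a group difference of 1.2 with standard deviation 2.0, we need to enroll 199 participants into each of the two comparison groups", a total of 398. The assumptions are 1:1 allocation between pre-operative education and pre-operative intervention, and that "within-subject observations follow AR(1) correlation pattern with a correlation coefficient of 0.7, and a missing completely at random rate of 5% each day". No alpha or power is given for this calculation.

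The number of repeated measures comes from Primary outcome measures: the BPI is completed daily for 14 days after discharge. Under Primary efficacy outcomes, Hypothesis 1 pools arms 2 and 4 against arms 1 and 3 and calls the GEE model a further primary analysis.

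The other two calculations give 24 per arm (80% power) or 31 (90%) for rate of recovery, and 35 per arm (80%) for the 3-month outcomes. The section then says "The target complete sample is 400 adolescent/parent dyads", with 500 to be enrolled to allow for 20% attrition.

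**The concern.** A difference of 1.2 with SD 2.0 is a standardised effect of 0.6, which needs well under 100 per group even with a single measurement per person. Averaging 14 correlated diaries should lower that number. A requirement of 199 per group therefore looks impossible on its face.

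This matters because the figure relates to a primary analysis and is the only one that leads to a total near 400. If it is wrong, the size of the trial is not justified by anything printed. If it is right, the printed difference or another input is wrong, and readers, including the monitoring board and anyone interpreting a null result, are given the wrong target effect.

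**Working it through.** **Inputs.** From Sample size and power calculations: difference 1.2, SD 2.0, AR(1) correlation 0.7, 5% of diaries missing completely at random each day, two equal groups. From Primary outcome measures: 14 daily diaries. Assumed, because not stated: two-sided alpha 0.05, with power 80% or 90%.

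**Step 1: variance of the 14-day mean.** The 14 × 14 AR(1) correlation matrix with 0.7 sums to 63.88. The variance factor relative to one day is f = 63.88 / 14² = 0.326. With 5% missing and an independence working correlation it becomes

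f = [14 × 0.95 + 0.95² × (63.88 − 14)] / (14 × 0.95)² = 0.330.

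With an AR(1) working correlation it is 0.306.

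**Step 2: attempt to reproduce the stated n.** n per group = 2 (z₀.₉₇₅ + z_power)² × SD² × f / difference².

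- 80% power: 2 × 7.849 × 4 × 0.330 / 1.44 = 14.4, so 15.
- 90% power: 2 × 10.507 × 4 × 0.330 / 1.44 = 19.3, so 20.

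Using t quantiles gives 16 and 21; an AR(1) working correlation gives 14 and 18. The stated 199 is not reproduced. It is 199/20 ≈ 10 to 199/15 ≈ 13 times the requirement.

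**Step 3: other readings of the same inputs.** Two-sided 5% unless noted.

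| Reading | n per group, 80% | n per group, 90% |
|---|---|---|
| AR(1) 0.7, 14 days, 5% missing | 15 | 20 |
| Exchangeable correlation 0.7, 14 days | 32 | 43 |
| AR(1) 0.7, 7 days | 23 | 31 |
| One measurement per person (f = 1) | 44 | 59 |

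Raising power to 99% gives 34 for the stated structure and 103 for a single measurement. The most extreme two-group variant tried (single measurement, alpha 0.01, 99% power, inflated for 20% attrition) gives 168, still below 199.

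**Step 4: what 199 per group delivers.** The standard error of the time-averaged difference is √(2 × 4 × 0.330 / 199) = 0.115. A true difference of 1.2 is about 10.4 standard errors, so power is essentially 100%. The detectable difference is 2.802 × 0.115 = 0.32 (80%) or 3.242 × 0.115 = 0.37 (90%).

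**Step 5: what SD would make 199 right for a difference of 1.2.** About 7.4 at 80% power (7.5 ignoring missing diaries) or 6.4 at 90%. The BPI runs from 0 to 10, where an SD cannot exceed about 5.

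**Step 6: the other calculations against N = 400.** Rate of recovery: 2 × 31 = 62. Chronic outcomes: 4 × 35 = 140. The 35 does not reproduce either: 1.0 with SD 1.8 at 80% power needs 2 × 7.849 × 3.24 / 1 = 50.9, so 51 per arm (52 with t quantiles). Even 4 × 52 = 208 is far from 400.

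**The case against.** The strongest objection is that the error runs towards oversizing. If 1.2 and 2.0 are right, the comparison has near-certain power, and no analysis, population or enrolment figure has to change. That is true and limits the harm, but it does not make the printed figures consistent.

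Second, the article never says that this calculation sets N. It lists three calculations and then states 400 separately, and its 199 is described as a number to enrol whereas 400 is a number of completers. The link is therefore an inference from 398 lying next to 400. That stands, and N may rest on reasoning not printed. For example, the chronic inputs with 90% power and a Bonferroni correction for six tests (three Hypothesis 3 contrasts on two outcomes) need about 100 per arm, or 400 in all. The article states no such adjustment, and that reading would not rescue the 199.

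Third, the documents do not show which number is wrong: the difference, the SD, the correlation or the 199 itself. This also stands. A difference of 0.36 with SD 2.0 gives 199 at 90% power under an AR(1) working correlation, so a misreported difference is possible but not established.

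Finally, a condensed article may leave alpha and power to a fuller document. Agreed, but no conventional choice of either closes a tenfold gap.

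**Conclusion.** The concern holds. The stated inputs and the stated 199 per group cannot all be correct. At two-sided 5% the inputs require about 15 per group for 80% power and 20 for 90% (14 to 21 across working correlation and t or normal quantiles). Conversely, 199 per group detects 0.32 to 0.37 points, roughly a quarter to a third of the printed 1.2. Alpha and power are assumed, but the conclusion does not depend on them, because even a single measurement per person at 99% power needs only 103.

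Power for the pooled pre-operative comparison is not at risk. What fails is the stated justification of the trial's size, since no other printed calculation comes near 400. Because the figure belongs to a primary analysis and is the only visible support for N, it must be corrected.

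**What to change.** Re-run this calculation and restate it with its alpha and power. Two routes are open:

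- If the difference, SD or another input was misreported, correct it so that 199 follows.
- Otherwise, keep N = 400 and report what it detects at two-sided 5%. For the 14-day average in the pooled pre-operative comparison this is about 0.32 BPI points (80% power) or 0.37 (90%). For a comparison of two single arms at 3 months, with 400 / 4 = 100 per arm and SD 1.8, it is about 0.72 or 0.83 points (t-based; the normal formula 1.8 × √(2/100) × 2.802 gives 0.71 at 80%), before any multiplicity adjustment.

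In either case, state which calculation sets N, and re-check the 35 per arm while the section is open. The cost is a rewrite of the sample-size section; enrolment does not change.
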